
### Outcomes

The primary outcome from this study is the proportion of patients who experience a postoperative major in-hospital complication or death (composite outcome). Secondary outcomes include: the proportion of patients who experience each component of the primary composite outcome (in-hospital mortality, intensive care unit admission, vascular complications, serious infections, protracted delirium); the proportion of patients who die or are readmitted within 30-days of initial discharge; length of hospital stay; discharge location; requirement for an alternative level of care upon discharge; quality of life; functional, cognitive and nutritional status; and health care resource utilization and costs.

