## Abstract

**Background:**

It is estimated that seniors (≥65 years old) account for >50 % of acute inpatient hospital days and are presenting for surgical evaluation of acute illness in increasing numbers. Unfortunately, conventional acute care models rarely take into account needs of the elderly population. The failure to consider these special needs have resulted in poor outcomes, longer lengths of hospital stay and have likely increased the need for institutional care. Acute Care for the Elderly models on medical wards have demonstrated decreased cost, length of hospital stay, readmissions and improved cognition, function and patient/staff satisfaction. We hypothesize that specific Elder-friendly Approaches to the Surgical Environment (EASE) interventions will similarly improve health outcomes in a cost-effective manner.

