**Methods/design:**

Prospective, before-after study with a concurrent control group. Four cohorts of 140 consecutively-screened older patients (≥65 years old) will be enrolled (560 patients in total). The EASE interventions involves co-locating all older surgical patients on a single unit, involving an interdisciplinary care team (including a geriatric specialist) in the development of individual care plans, implementing evidence-informed elder-friendly practices, use of a reconditioning program, and optimizing discharge planning. Subjects will be followed via chart review for their hospital stay, and will then complete in-person or telephone interviews at 6 weeks and 6 months after discharge. Measured outcomes include clinical (postoperative major in-hospital complication or death [primary composite outcome]; death or readmission within 30-days of initial discharge; length of hospital stay), humanistic (quality of life; functional, cognitive, and nutritional status) and economic (health care resource utilization and costs) endpoints. Within-site mean change scores will be computed for the composite primary outcome and the overall covariate-adjusted between-site pre-post difference will be the dependent variable analyzed using generalized linear mixed model procedures including adjustment for clustering.

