### Aim & objectives

The aim of the EASE study is to assess the impact of an elder-friendly surgical unit, with the goal of delivering evidence-informed care to improve the quality of care to older acute surgical patients, in order to reduce unnecessary health care resource utilization. The EASE study will realign current resources, implement evidence-informed practices, and improve health outcomes in a cost-effective manner.

The specific objectives of the EASE Study are to:Assess the clinical effectiveness of the EASE initiatives in reducing the rate of post-surgical complications, in-hospital mortality and length of stay, compared to controls.Determine if the EASE initiatives improves humanistic outcomes including health-related quality of life (HRQL), functional capacity and patient satisfaction, compared to controls.Determine the incremental cost and cost-effectiveness of the EASE initiatives.

In aggregate, these objectives will assess the program’s impact on a comprehensive range of outcomes important to patients, providers, and policy-makers.

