### Interventions

The EASE initiative will involve:**Capacity re-alignment:** elderly surgical patients are currently scattered across different nursing units. Patients will be co-located on 1 unit to allow better implementation of the initiatives and coordination of care.**Interdisciplinary care delivery:** will include daily ward rounds by geriatric specialists, in addition to consultation with rehabilitation providers, pharmacists, dieticians and social workers within 24 h of admission to help in the development of individual care plans.**Implementation of evidence-informed practices:** optimizing evidence-based guideline adherence, such as:Medication review and reconciliationEarly mobilization on the surgical unitPrevention of postoperative complications (e.g. venous thromboembolism prophylaxis)Incorporation of Enhanced Recovery After Surgery program principles such as early feeding following surgery, reduced use of total parenteral nutrition, and avoidance or early removal of tubes [nasogastric, urinary catheters], drains, and lines [intravenous, central lines] [42].Elder-friendly practices such as comfort rounds, performed every 2 h by the nursing staff to address unmet care needs, mobility, nutrition, pain management, and prevention of falls and delirium.Health care provider/patient/family education**Reconditioning program:** a targeted, functional program that patients can perform independently at their bedside, beginning immediately post-operatively.**Transition optimization:** the interdisciplinary teams (from 2 above) will define the optimal blend of patient-specific services required to support safe, quality transitions to discharge with a goal to maximize functional recovery and return to baseline health status. This coordinated plan will be established at admission and will include appropriate discussions with the patients and caregivers.

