### Data collection

Study personnel will collect data using standardized case report forms recorded on an electronic database using a secure, internet-based portal.**Socio-demographic information (baseline)**: including age, sex, ethnicity, body mass index, medical comorbidities, residence prior to admission, blood pressure, heart rate, respiratory rate, haemoglobin, creatinine and medication history. Data obtained from chart review will be used to create the Charlson comorbidity index [43] and Rockwood’s frailty index [44].**Hospitalization details (baseline):** including admitting diagnosis, operative procedure, operating surgeon, American Society of Anaesthesiologists Class, requirements for alternative service consults, total parenteral nutrition and urinary catheter utilization, discharge location, and any new requirement for alternative level of care upon discharge.**Major in-hospital complications (baseline):** all complications are defined using the Centers for Disease Control definitions [45], including:Intensive care unit admission (includes respiratory failure, cardiac arrest or septic shock),Vascular complications (myocardial infarction, stroke, deep venous thrombosis, pulmonary embolism)Serious infections (pneumonia, intra-abdominal abscess, urinary tract infection, deep wound infection or infected decubitus ulcer), andProtracted delirium (≥48 h). A validated chart-based method for identification of delirium will be utilized [46]. This chart-based instrument has a sensitivity of 74 % and a specificity of 83 %, using the Confusion Assessment Method [47] as the gold standard.**Mortality (baseline, 6 weeks, 6 months):** divided into in-hospital mortality, 30-day mortality and 6 month mortality.**Length of hospital stay (baseline):** divided into:acute length of stay defined as time until the acute medical treatment for that patient is complete;total length of stay which includes both medical treatment time and time awaiting transfer to another hospital (e.g., rural hospital) or alternative level of care (assisted living, long-term care placement or rehabilitation).**Readmission (6 weeks, 6 months):** divided into 30-day readmission and 6 month readmission.**Functional status (6 weeks):** including:Edmonton Frail Scale [48]: a valid and reliable tool to assess the frailty of the older patients. The scale has 11 items assessing cognition, general health status, functional independence, social support, medication use, nutrition, mood, continence and functional performance. Higher scores indicate greater frailty.Timed Up and Go [49]: a commonly used screening tool for falls risk. The patient is timed while they rise from an arm chair, walk three metres at a comfortable and safe pace, turn and walk back to the chair and sit down again. Faster time indicates a better functional performance.**Cognitive status (6 weeks):** using the Abbreviated Mental Test Score [50]. This 10 item test screens older patients for possible cognitive impairment, with lower scores indicating greater impairment.**Quality of life and health status (6 weeks and 6 months):**EQ-5D [51]: A widely used, validated, preference based generic HRQL instrument. It encompasses five domains of HRQL (mobility, self-care, usual activities, pain/discomfort, and anxiety/depression) and a visual analogue scale. The five health domains can be scored and totalled to yield a single Index (EQ-Index) score anchored between 0 (death) and 1 (full health). The visual analogue scale ranges from 0 to 100 with higher scores indicating better HRQL. The EQ-5D is also a measure of utility; a requirement for cost-effectiveness analyses.SF-12 [52]: A widely used, validated, generic HRQL instrument. It yields a physical and a mental health component summary score. Higher scores indicate better health status.**Nutritional status (6 weeks and 6 months):** using the Malnutrition Screening Tool [53]. This is a brief screening tool to assess nutritional status, with smaller scores indicating better nutritional status.**Health care resource utilization and costs (baseline and 6 months):** Health care resource utilization will be assessed through financial micro-costing databases. A modified health resource utilization questionnaire [54] will be administered at the final follow up visit to identify patient out-of-pocket expenses and indirect carer costs.

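### The primary composite is counted only during the index stay, which EASE aims to shorten, so earlier discharge can lower the observed rate without fewer complications

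*Protocol article*

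**What the plan says.** The Outcomes section of the protocol article defines the primary outcome as "the proportion of patients who experience a postoperative major in-hospital complication or death (composite outcome". Two further statements fix its window as the index stay:

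- The secondary outcomes include "each component of the primary composite outcome (in-hospital mortality, intensive care unit admission, vascular complications, serious infections, protracted delirium", so the death component is also death in hospital.
- Data collection lists "Major in-hospital complications (baseline" at the baseline time point only; the 6-week and 6-month contacts are not named for complications. The abstract agrees: "Subjects will be followed via chart review for their hospital stay".

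No window in days from surgery is given for the composite.

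On the stay itself, the first objective (Aim & objectives) is to assess EASE in "reducing the rate of post-surgical complications, in-hospital mortality and length of stay, compared to controls". The abstract says of the parent model on medical wards that such units "have demonstrated decreased cost, length of hospital stay, readmissions and improved cognition, function and patient/staff satisfaction".

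Some data do reach past discharge. Mortality is "divided into in-hospital mortality, 30-day mortality and 6 month mortality", readmission is recorded at 30 days and 6 months, and death or readmission within 30 days of discharge is a secondary outcome.

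**The concern.** The time during which a patient can contribute a primary event equals the length of that patient's stay. If EASE shortens the stay as intended, cohort (ii) is observed for less time than the other three cohorts. An infection, a thrombosis or a death that would have fallen on a later ward day is then not counted if the patient has already gone home. With event timing unchanged, a shorter stay can only lower the count or leave it as it was, so any bias favours EASE.

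The planned analysis does not protect against this. A difference of differences removes fixed site differences and time trends common to both sites. A stay shortened by EASE is specific to one site in one period, which is exactly the contrast being estimated. Adjusting for length of stay would not help either: stay is affected by the intervention, and complications themselves prolong it.

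At stake is the reading of a favourable primary result, which could reflect fewer complications, a shorter counting period, or both.

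**Working it through.** The plan gives no figure for this effect, so there is none to reproduce. The calculation below only shows an order of magnitude.

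**Inputs from the article (Sample size calculation).** Primary event rate pre-EASE 35%; minimal important difference 10 points.

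**Inputs assumed, not in the article.** Stay L = 14 days (range 10 to 18); reduction d = 2 days (also 1 and 3); no true effect on complications; the same stay and the same cut for every patient; every uncounted event merely moved past discharge.

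**Formula.** Let the cumulative hazard over the full stay be H = −ln(1 − 0.35) = −ln(0.65) = 0.431. With Weibull shape k, the risk counted in a stay of L − d days is 1 − exp{−H × ((L − d)/L)^k}. Shape k = 1 is a constant hazard; k = 0.5 is front-loaded.

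**L = 14, d = 2.**
- k = 1: 0.431 × 12/14 = 0.369; 1 − exp(−0.369) = 0.309. Fall of 4.1 points.
- k = 0.5: 0.431 × √(12/14) = 0.399; 1 − exp(−0.399) = 0.329. Fall of 2.1 points.
- k = 0.25: 0.431 × (12/14)^0.25 = 0.414; 1 − exp(−0.414) = 0.339. Fall of about 1.1 points.

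**Other assumed values.**

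| Stay L (days) | Cut d (days) | Constant hazard | Weibull 0.5 |
|---|---|---|---|
| 14 | 1 | 2.0 points | – |
| 14 | 3 | 6.3 points | 3.3 points |
| 10 | 2 | 5.8 points | 3.0 points |
| 18 | 2 | 3.2 points | 1.6 points |

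**A version without a hazard model.** If a share q of events moves past discharge, the counted rate is 0.35 × (1 − q). For q = 5%, 10% and 20% the fall is 1.8, 3.5 and 7.0 points. To produce the whole 10 points as an artefact, q would have to be 10/35, about 29%. Under constant hazard the stay would have to fall by 1 − ln(0.75)/ln(0.65), about 33%.

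**Effect on the test.** Take a 3.5-point artefact, no true effect, 140 patients per cohort and an unadjusted two-sided z test. The standard error is √[(3 × 0.35 × 0.65 + 0.315 × 0.685)/140] = 0.080, and the rejection rate is about 7% instead of 5%. In this example the harm lies mainly in a biased estimate, less in false significance.

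**The case against.** Several points on the other side stand.

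- **Complete ascertainment.** In-hospital counting by chart review is the reason the Sample size section can expect no drop-outs for the primary outcome. The same section anticipates high attrition at follow-up, and the consent exemption covers only the in-hospital chart review. Moving the primary outcome past discharge would put that completeness at risk.
- **Size.** The illustration rests on assumed stays and hazards. Its lowest tabulated value, 1.6 points, is no lower bound, as the k = 0.25 result shows. Patients sent home sooner may be those at least remaining risk, and saved days may be days spent waiting for placement; either could shrink the effect.
- **Not all of it is artefact.** The Background describes hospital itself as a source of infection, delirium and other insults, so earlier discharge may truly prevent some events. Fewer complications would also shorten the stay.
- **Existing safeguards.** Displaced events that cause death or readmission would show in the 30-day secondary outcome, which is also analysed as a difference of differences. This mitigates the problem. It is no cure, because that outcome starts at discharge, is never combined with in-hospital events, and misses complications treated without readmission.

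A reader might also infer that the transition component is meant to cut the stay. The Interventions section does not say so: it speaks of services "required to support safe, quality transitions to discharge with a goal to maximize functional recovery and return to baseline health status". The explicit aim of a shorter stay is in the first objective.

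**Conclusion.** The point holds as a design caution. The outcome is limited to the stay, the stay is a stated target of the intervention, and the bias, where present, favours EASE and survives the difference of differences. Its size is unknown, since the article reports neither length of stay nor event timing. About 2 to 4 points for a 2-day cut from an assumed 14-day stay is an illustration only, and smaller values are plausible.

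Two stronger readings are tempting and not supported. One is that earlier discharge does lower the rate: the documents support only that it can. The other is that benefit and earlier discharge cannot be separated at all: the planned 30-day outcome, the mortality data, the component results and length of stay give partial information. What is missing is one analysis that observes every patient for the same time from surgery.

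**What to change.** Keep the in-hospital composite as primary, and pre-specify the following:

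1. A supportive difference-of-differences analysis, with the same model, of a fixed-window composite for every patient: in-hospital major complication or death up to day 30 from surgery, plus death or all-cause readmission after discharge up to day 30 from surgery.
2. Its result reported beside the primary result and length of stay.
3. A rule that a primary benefit is not attributed to fewer complications if the fixed-window result does not point the same way.

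The ingredients are the mortality and readmission data already planned. Discharge cannot precede surgery in these postoperative patients, so day 30 from surgery never falls later than day 30 from discharge. The post-discharge period already foreseen therefore covers the new window, provided the dates of surgery, complications, death and readmission are recorded.

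The cost is a paragraph of outcome and analysis text and some recoding. There are three downsides. All-cause readmission is less specific than readmission for a complication, but the article does not list the reason for readmission as collected. Post-discharge events treated without readmission are still missed, so the bias is reduced, not removed. Capture after discharge may be less complete than on the ward, so completeness should be reported for each of the four cohorts.

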### Data analysis

We will evaluate the effectiveness of the EASE initiative implementation by comparing between-site mean changes in each outcome in the cohort of patients hospitalized from the baseline cohort (defined as “pre-EASE”) to those hospitalized after implementation (defined as “post-EASE”).

Initially, exploratory data analysis will be performed on each major variable, including calculation of means, medians, proportions, and measures of central tendency. Baseline variables pre-EASE and post-EASE will be compared between sites using *X*^2^ tests for categorical variables, Student T-tests for normally distributed continuous variables, and the Wilcoxon rank sum test for non-normally distributed variables.

Secondly, within-site mean change scores will be computed for the composite primary outcome (difference of proportions) and the overall covariate-adjusted between-site pre-post difference (‘difference of differences’) will be the dependent variable analyzed using generalized linear mixed model procedures and will include adjustment for clustering by study site and operating surgeon. The regression model will be constructed using recommended techniques and assessment of model assumptions (including tests of normality, tests of colinearity and log-transformation of non-normally distributed continuous variables) will be performed as necessary. Additional adjustment for baseline age, sex, BMI, ethnicity, blood pressure, heart rate, respiratory rate, haemoglobin, creatinine, admitting diagnosis, medical comorbidities, operative procedure, Rockwood clinical frailty score, Charlson comorbidity index, American Society of Anaesthesiologists class, baseline month of enrolment, and/or baseline place of residence will be performed. Secondary endpoints will be analyzed as ‘difference of differences’ in a manner similar to that outlined for the primary outcome.

For cost analysis, exploratory baseline analyses will be completed including calculation of mean index hospitalization cost, median index hospitalization cost, mean readmission cost, median readmission cost and measures of central tendency for both variables. The cost of the intervention will also be calculated and included in the total cost post-EASE. All costs pre-EASE and post-EASE will be compared between sites. The difference in costs between sites will be calculated and compared. If required, a risk-adjustment model to predict cost differences between sites will be developed. A cost per quality adjusted life year (QALY) gained will also be calculated. The mean cost difference in each site will be divided by the QALYs achieved in each site. QALYs will be calculated using the utility values measured by the EQ-5D and the length of life of each patient.

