### Sample size calculation

Based on our pilot data, we anticipate the incidence of the primary composite outcome to be 35 % pre-EASE (cohorts (i) and (iii)) [55–57]. A 10 % absolute difference in the primary endpoint is considered to be the minimal clinically important difference to detect (a commonly used threshold for many interventions [58]). Accordingly, assuming an alpha = 0.05, beta = 0.2 (80 % power), a 15 % decline in the primary outcome post-EASE, a 5 % decline in the primary outcome in the control group (10 % absolute overall ‘difference of differences', 1:1 recruitment of cases to controls), we will require 140 patients per centre (UAH, Edmonton and FMC, Calgary) or 280 patients total. Since all enrolled patients will be followed by chart review to ascertain the primary outcome, there will be no drop-outs and no sample size adjustment will be required for attrition. However, a priori, we have decided to double the required sample size (280 patients per site or 560 in total) to account for the likelihood of high attrition at follow up. Given the absence of previous studies, after collecting data on the first 140 patients (total of both sites), we will calculate an updated sample size calculation.

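### The primary mixed model names the single between-site difference of differences as its response, but that is the contrast to be estimated, and no model can be fitted to it

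*Protocol article*

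**What the plan says.** The Outcomes section defines the primary endpoint as "the proportion of patients who experience a postoperative major in-hospital complication or death (composite outcome"), so each patient either has the event or does not. The Abstract gives the layout: "Four cohorts of 140 consecutively-screened older patients (≥65 years old) will be enrolled (560 patients in total"). Study design splits these into a before and an after cohort at each of two hospitals.

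The Data analysis section first states that "within-site mean change scores will be computed for the composite primary outcome (difference of proportions"). It then says that the adjusted contrast between the sites in these changes "will be the dependent variable analyzed using generalized linear mixed model procedures", and that the analysis "will include adjustment for clustering by study site and operating surgeon". Seventeen baseline covariates are listed for adjustment, and secondary endpoints are to be handled in a similar way. The Abstract (Methods/design) carries the same construction, beginning "Within-site mean change scores will be computed for the composite primary outcome".

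The Sample size calculation gives the planning values. On the event rate, "we anticipate the incidence of the primary composite outcome to be 35 % pre-EASE" at both sites. On the target, "A 10 % absolute difference in the primary endpoint is considered to be the minimal clinically important difference to detect".

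**The concern.** The response of a regression model has to vary over the units analysed. Here the named response is a summary of the whole study: one number formed from four cohort proportions. The sentence is also circular, because a covariate-adjusted difference is what a model produces and so cannot be what goes into it.

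The text names a response, and names the wrong quantity, so this is not a detail left for another document. The sentence defines the primary analysis and, by extension, the secondary ones. Anyone carrying it out must replace it with something else. Unless the replacement is written down beforehand, its form (unit of analysis, treatment of site, reported effect measure) is settled outside the protocol and possibly after the data are seen.

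**Working it through.** **Inputs.** From the article: 2 sites, 4 cohorts of 140, 560 patients (Abstract, Study design); a binary composite per patient (Outcomes); 17 listed covariates, by my count (Data analysis); 35% before at both sites, with declines of 15 points (intervention) and 5 points (control) (Sample size calculation). My own assumption, not the protocol's: the unequal baseline rates in step 5.

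**1. The plan's own target.** The after-period rates are 35 − 15 = 20% (intervention) and 35 − 5 = 30% (control). The difference of differences is (20 − 35) − (30 − 35) = −15 + 5 = −10 points. This reproduces the stated 10-point absolute target.

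**2. How many values the named response has.** Four proportions give two within-site changes, and two changes give one difference D. With D as the response, an intercept alone uses the only degree of freedom: 1 − 1 = 0 remain. There is no residual variance and hence no standard error, and nothing from which to estimate 17 covariate effects or a surgeon variance. Using the two within-site changes as the response does not help: with an intercept and a site term, 2 − 2 = 0 remain.

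**3. The same contrast from patient-level data.** Let Y be a patient's composite (0 or 1) and g a link function:

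g(P(Y = 1)) = b0 + b1·site + b2·period + b3·(site × period) + covariates + surgeon effect.

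This uses 560 responses. With an identity link, D is b3. With a logit link, D is obtained from the four model-based risks. The uncertainty comes from variation among patients. Under the planning rates, ignoring covariates and surgeon:

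SE(D) = √[(0.35×0.65 + 0.20×0.80 + 0.35×0.65 + 0.30×0.70)/140] = √(0.825/140) = 0.0768, or about 7.7 points.

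A model that takes D itself as its response discards exactly this information.

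**4. Clustering by site.** A variance between sites would be estimated from 2 sites, that is on 2 − 1 = 1 degree of freedom. That is too little for a random effect. A fixed site effect removes the constant difference between the hospitals without needing a variance.

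**5. Whether the scale matters.** In the plan's scenario the odds ratios are (0.20/0.80)/(0.35/0.65) = 0.464 (intervention) and (0.30/0.70)/(0.35/0.65) = 0.796 (control). Their ratio is 0.464/0.796 = 0.583, in the same direction as −10 points. If both sites start at 35% and D = 0, they also end at the same rate, so the ratio of odds ratios is exactly 1.

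The scales separate only when baselines differ. Two illustrations under assumed rates:

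| Intervention | Control | D | Ratio of odds ratios |
|---|---|---|---|
| 45 → 35% | 25 → 15% | 0 points | 0.658/0.529 = 1.24 |
| 40 → 30% | 30 → 20% | 0 points | 0.643/0.583 = 1.10 |

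**The case against.** The strongest reply is that the intent is plain. Generalized linear mixed models, patient-level covariates and surgeon clustering make sense only with a patient-level response, so the phrase is a misnomer for the estimand in a condensed article. As a reading of intent this is right, and it is why the repair is easy. It does not make the sentence correct. The Abstract and the Data analysis section both state it, and the secondary endpoints inherit it.

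Three stronger readings are tempting, and the document does not support them.

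- A reader might infer that the effect scale conflicts with the 10-point target. It does not. The Data analysis section speaks of a difference of proportions and the Sample size calculation of an absolute difference, which is the same scale. No logit link or odds ratio is mentioned, and an unstated link is something an article may leave to fuller documents. The ratios of 1.24 and 1.10 need unequal baselines, whereas the plan anticipates 35% at both sites and describes their patients as similar. They illustrate a possibility and do not measure an error in the text.
- A reader might infer that normality checks and log-transformation are to be applied to the binary composite. The text limits the transformation to continuous variables, which fits covariates such as creatinine and outcomes such as length of stay.
- A reader might object that no patient has a before and an after value, so change scores are invalid. The plan computes changes in cohort proportions within each site, and these are legitimate summaries.

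**Conclusion.** The point holds for the response variable. As written, the primary model has one response value where the design supplies 560, and it cannot be fitted. This follows from the layout of two sites and four separately recruited cohorts and needs no assumption about event rates. Treating site as a random cluster is likewise unsupported with two sites.

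On scale the conclusion is narrower: once the model is rewritten, its reported effect should be tied explicitly to the absolute scale that the protocol already uses. Under the protocol's equal baselines a null effect is null on either scale. The tie guards against site differences that may appear, since the sites are not randomised.

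The error is one of wording with a clear remedy, but it sits in the definition of the primary analysis and should be corrected before the data are analysed. Whether the sample size suits a difference of differences is a separate question that this point does not address.

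**What to change.** Replace the sentence in the Data analysis section, and its counterpart in the Abstract, with a statement along these lines:

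- **Response:** each patient's binary composite, 560 records.
- **Fixed effects:** site, period, site-by-period, and the listed baseline covariates.
- **Random effect:** operating surgeon. Say openly that the fixed site effect replaces clustering by study site.
- **Primary estimate:** the site-by-period contrast as an adjusted risk difference with a confidence interval, read against the 10-point target. One route is a logistic model with marginal standardisation: average the predicted risk for each of the four site-period combinations over the same patients, take the difference of differences of those four risks, and obtain the interval by the delta method or bootstrap. An identity link is an alternative.
- **Secondary endpoints:** the same structure, with each patient's own value as the response and a link suited to the outcome.

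The within-site differences of proportions can stay as descriptive summaries, and the log-transformation wording for continuous variables needs no change. The cost is a rewording of the analysis text, with no change to design, data collection or enrolment.
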